### Randomisation and allocation concealment

To prevent the potential risk of treatment contamination within the ED, randomisation will not be performed there. Instead, the research assistant (RA) will input baseline data collected at the ED directly into the web-based trial entry form linked to a computerised database. Subsequently, randomisation will be performed at the principal investigator's institution by an independent statistician who will have no other involvement in the study. Stratified block randomisation with 1:1 allocation will be conducted using varying block sizes of 4–10 to achieve an appropriate balance of participant numbers between the intervention and control groups and to optimise allocation concealment.

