### **Sample size**

We used G\*Power to estimate the sample size based on the results of our pilot study conducted at an ED and a previous study using a brief smoking cessation intervention based on self-determination theory. The results of the pilot study showed an approximately 12% between-group difference in successfully adopting at least one healthy lifestyle at 6 months (the primary outcome of this proposed project). However, we opted for a more conservative effect size for our sample size calculation. Based on our previous large-scale RCT on a brief smoking cessation intervention based on self-determination theory, we expect a between-group difference of at least 5% ( $\geq 10\%$  in the intervention group vs.  $\leq 5\%$  in the control group) in the primary outcome at 6 months. To detect a significant between-group difference with a power of 80% at a significance level of 5% (two-tailed) in the proportion of participants modifying their health risk behaviours and/or adopting healthy lifestyles, 435 participants will be needed per group. To account for a potential attrition rate of 30% at the 6-month follow-up, we will recruit a total of 1,242 participants.

Based on the number of EDs visits (1.8 million) in Hong Kong between 2021 and 2022, we are confident that we will be able to recruit the required number of participants within 18 months.

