### **Data processing and analysis**

#### **Instruments:**

We will use available objective assessment tools to supplement the participants' self-reported outcomes to determine changes in their health-risk behaviours after the intervention. For verifying smoking cessation, we will use the biochemically validated 7-day point prevalence of abstinence, determined by a saliva cotinine level of  $<115$  ng/ml and an exhaled carbon monoxide level below  $<4$  ppm. Only those who meet both these criteria will be regarded as biochemically validated abstinent individuals; otherwise, the participants will be considered to have failed the validation. HK\$200 supermarket coupon being the incentive for completing biochemical validations

**A behavioural risk-factor questionnaire** will be used as the patient-report outcome measure to collect data on eligible participants' demographic and health-risk behaviours (tobacco use, binge drinking, unhealthy diet and physical inactivity) at baseline and at 3, 6, and 12 months. Moreover, participants' blood pressure and body mass index will be documented. This questionnaire was used to investigate multiple health-risk behaviours among Chinese adults in Hong Kong in 2021.

**The EuroQoL 5-Dimension 5-level (EQ-5D-5L)** will be used to assess the participants' health-related quality of life at baseline, 6 months, and 12 months. The psychometric properties of the Chinese version of the EQ-5D-5L were tested, and the findings indicate that this tool is a valid, reliable, and sensitive measure of health-related quality of life. A Chinese-specific EQ-5D-5L value set will enable the calculation of health utility scores applicable to the Chinese population and quality-adjusted life-years (QALYs) for conducting cost-effectiveness analysis.

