### **Data Analysis**

The baseline characteristics of the two groups will first be compared using the chi-square test for categorical variables and analysis of variance for continuous variables. An intention-to-treat analysis will be used by imputing all non-responses at follow-up by baseline values (i.e. assuming failure or no change after the intervention), to yield more conservative effect size estimates.

SPSS for Windows (SPSS version 26.0; IBM Corp., Armonk, NY, USA) will be used for the quantitative data analysis. Descriptive statistics will be used to calculate the mean, standard deviation, and frequency of the demographic and health-risk behaviour data. The primary analysis including the main effect, i.e., behavioural changes at 6 months in the intervention group versus those in the control group, will be performed using a chi-square test or Fisher's exact test. The secondary analyses will (1) assess the main effect adjusted for baseline differences, (2) assess the secondary outcomes (health-related quality of life) at 6 and 12 months, and (3) construct a generalised estimating equation model (GEE). The GEE model will be used to calculate the adjusted odds ratios for the self-reported the number of healthy lifestyles engaged in, after adjusting for the baseline demographic and clinical characteristics that show significant differences, and the within-subjects effect of the repeated-measure outcomes (6 and 12 months).

We will conduct a cost-effectiveness analysis (CEA) using standard methods. The CEA will be populated using empirical 12-month RCT data. An ingredients approach will be used to estimate the cost of the intervention programme, including that of the intervention material (e.g., leaflets and videos), the administration cost, and the time taken to deliver the intervention. The health effectiveness outcomes will include the number of participants who have adopted healthy lifestyles at 6 and 12 months and their QALYs.

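### The secondary adjusted analyses choose their covariates by baseline significance tests, so chance imbalance rather than prognosis sets the model

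*Protocol*

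**What the plan says.** All the relevant text is in the protocol's Data Analysis section, apart from the allocation method.

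- The first step is a between-arm test of baseline data: "The baseline characteristics of the two groups will first be compared using the chi-square test for categorical variables and analysis of variance for continuous variables". No significance threshold is given for these tests.
- The primary comparison at 6 months is unadjusted; it "will be performed using a chi-square test or Fisher's exact test".
- The first secondary analysis is to "assess the main effect adjusted for baseline differences". The wording is looser: it does not mention significance and lists no covariates.
- The third secondary analysis is a GEE giving adjusted odds ratios for the number of healthy lifestyles at 6 and 12 months, after "adjusting for the baseline demographic and clinical characteristics that show significant differences".
- Quality of life is a separate secondary item, with no covariate rule stated.
- The section on randomisation says: "Stratified block randomisation with 1:1 allocation will be conducted using varying block sizes of 4–10". It does not name the stratification factors.

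No covariate is fixed in advance for any adjusted model.

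**The concern.** Allocation is random, so a significant baseline difference reflects chance. Its p-value says nothing about whether the variable predicts the outcome. A rule built on it fails in two directions: it admits variables that do not matter, and it leaves out variables that do unless they happen to be imbalanced.

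The variable most exposed is the baseline number of risk behaviours, which is tied to the outcome by design. Eligibility requires at least one risk behaviour, and Appendix 1 defines success behaviour by behaviour. A participant with one risk behaviour can therefore newly adopt at most one healthy lifestyle, while a participant with four can adopt four. Missing follow-up values are replaced by baseline values, which strengthens the link for the number of lifestyles engaged in. Yet the rule adjusts for this variable only if the arms happen to differ on it.

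At stake is the credibility of the adjusted results. Their covariates are settled after the data are in, and the looser wording of the first secondary analysis leaves further room for choice. The protocol states this rule outright, so it is not a detail left to a statistical analysis plan.

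**Working it through.** **1. The plan's own figure.** For 10% versus 5%, two-sided 5% and 80% power, with pooled variance under the null:

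n = [1.96·√(2 × 0.075 × 0.925) + 0.842·√(0.10 × 0.90 + 0.05 × 0.95)]² / 0.05² = 434.4, so 435 per group.

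Then 870/0.70 = 1,242.9, against the stated 1,242. The calculation reproduces and uses no covariates, so the rule does not bear on it.

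**2. Chance that at least one variable is selected by luck.** Assumptions: each baseline test is at 5%, and the k variables are independent. The probability is 1 − 0.95^k.

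| k | P(at least one selected) |
|---|---|
| 8 | 1 − 0.95^8 = 34% |
| 12 | 1 − 0.95^12 = 46% |
| 20 | 1 − 0.95^20 = 64% |

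**3. Chance that a given strong predictor is selected.** This is the size of its own baseline test, about 5%, however prognostic it is. A variable used as a stratification factor is balanced by design and would be selected even less often.

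**4. How much the baseline count may vary.** The survey in the Introduction found 80.3% with at least one risk behaviour and 47.0% with two or more. Among those with any, 47.0/80.3 = 59% had several. If ED attendees are similar, the baseline count will vary materially.

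**5. Simulation of the rule.** Settings: N = 1,242, 10 independent baseline variables of which one predicts the outcome, no treatment effect, 4,000 runs per setting. The outcome is continuous and the model linear, so this illustrates the mechanism and does not model the GEE. The correlations are assumptions.

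| Correlation with outcome | Predictor selected | SD of effect: unadjusted / rule / prespecified | Type I error: rule / prespecified |
|---|---|---|---|
| 0.3 | 4.6% | 0.056 / 0.055 / 0.053 | 4.6% / 4.4% |
| 0.5 | 5.0% | 0.057 / 0.055 / 0.049 | 4.3% / 5.0% |
| 0.7 | 5.3% | 0.057 / 0.053 / 0.040 | 3.6% / 4.8% |

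The Monte Carlo standard error of the error rates is about √(0.05 × 0.95/4,000) = 0.3 percentage points. The rule recovers little of the available precision and is, if anything, slightly conservative.

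**The case against.** The best case against the point concerns its reach, and much of it stands.

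- **The primary analysis.** It is an unadjusted test, so the rule cannot alter its p-value. This stands.
- **False positives.** A reader might infer that the rule inflates them. In a linear model with correlation 0.5, a baseline imbalance at z = 1.9 (p = 0.057) would go unadjusted, and the test statistic would be N(0.95, 0.75), giving P(|Z| > 1.96) = 12.2%. But that conditions on an imbalance chosen just below an assumed cut-off. The same formula gives 2.4% at z = 0 and 4.8% at z = 1, and the overall rate in the simulation was 3.6% to 4.6%. Inflation is not supported.
- **Quality of life.** A reader might also apply the rule to EQ-5D-5L and claim a 25% variance reduction (0.5²) from adjusting for its baseline. The quoted rule governs the GEE for lifestyles, not the quality-of-life item. Nor does that linear result carry over to a log odds ratio. This stands.
- **Harmless extras.** One irrelevant covariate among about 1,242 participants costs almost nothing. This is true; the larger cost is omitting the strong predictor.
- **Looser wording.** The phrase for the first secondary analysis could mean adjustment for baseline values. That is possible, but it follows the baseline tests and names no alternative. The GEE wording is not ambiguous.

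None of this defends choosing covariates by significance tests between randomised arms.

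**Conclusion.** The point holds for the secondary analyses: explicitly for the GEE and, in looser words, for the adjusted main-effect analysis. The model is unknown until the data are seen. Chance selection of at least one variable has a probability of 34% to 64% for 8 to 20 variables, and a strong predictor is left out about 95% of the time. The adjusted odds ratio is non-collapsible, so it changes meaning with the covariates drawn.

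The precision loss is modest to moderate. At correlation 0.5 the SD is 0.055 rather than 0.049, a variance ratio of (0.0549/0.0493)² = 1.24.

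These sizes rest on assumptions the protocol does not supply: a 5% baseline threshold, independent variables, their number, the correlation, and a linear model in place of the GEE. The protocol should be changed, but the trial's main conclusion does not depend on it.

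**What to change.** In Data Analysis, delete the last four words of the GEE clause quoted above and stop using baseline significance tests to select covariates. Baseline data can be shown descriptively by arm.

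Name one covariate set in advance for both the adjusted main-effect analysis and the GEE: baseline number of risk behaviours, age, sex and the stratification factors used in the randomisation. The section on randomisation must name those factors.

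As an extension beyond what the quoted rule covers, adjust the quality-of-life analysis for baseline EQ-5D-5L.

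The cost is a wording change plus naming the stratification factors. Baseline behaviours, demographics and EQ-5D-5L are already collected, and the sample size does not change. The change should be made before outcome data are seen.

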### **Ethical Concern**

This research project is in compliance with the Declaration of Helsinki.

To protect participants' privacy, all research data would be handled in line with HA / Hospital's policy in handling / storage / destruction of patients' medical records. They would be locked in cabinets to keep patients' information in confidential. Electronic data should be saved in secured computer with restricted access. The protocol complies with the Declaration of Helsinki. All research and personal data will be kept for 5 years upon study completion. All personal and study data will be used for the purpose of this study. It will be discarded in accordance to the prevailing data management policy after the aforesaid storage period.

**Appendix 1**

Criterion for determination of each health-risk behaviour and criteria of successful adopting a healthy lifestyle

| Behavioural risk factors  | Criterion of health-risk behaviour                                                                                                                                                                          | Successful criteria of adopting a healthy lifestyle                                                                                                                                               |
|----------------------------------|--------------------------------------------------------------------------------------------------------------------------------------------------------------------------------------------------------------------|----------------------------------------------------------------------------------------------------------------------------------------------------------------------------------------------------------|
| Tobacco use          | Smoked at least 1 cigarette a day over the past 30 days                                                                                                                                                            | Self-reported 7-day point prevalence of smoking abstinence                                                                                                                                               |
| Binge drinking       | Reporting $\geq 1$ binge drinking episodes (consumption of five or more alcoholic beverages on one occasion) in the past month.                                                                                    | Self-report no binge drinking episode (consumption of five or more alcoholic beverages on one occasion) in the past month.                                                                               |
| Unhealthy diet       | Have consumed less than five servings of fruit and vegetables per day or have had a daily intake of less than 400 grams of fruit and vegetables                                                                    | Have consumed at least five servings of fruit and vegetables per day or have had a daily intake of at least 400 grams of fruit and vegetables                                                            |
| Physical inactivity  | (1) Performed less than 150 minutes of moderate-intensity aerobic physical activity throughout the week, or (2) performed less than 75 minutes of vigorous-intensity aerobic physical activity throughout the week | Performed at least 150 minutes of moderate-intensity aerobic physical activity throughout the week, or performed at least 75 minutes of vigorous-intensity aerobic physical activity throughout the week |

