#### **Outcome measures:**

The **primary outcome** will be the number of healthy lifestyles adopted at 6 months. The criteria of successful adopting a healthy lifestyle are presented in Appendix 1.

**The secondary outcomes** will be the number of healthy lifestyles adopted at 12 months and improvement in health-related quality of life at 6 and 12 months.

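### Quitting is to be verified biochemically, but the primary outcome scores tobacco success by self-report, so a claimed quitter whose test refutes the claim still counts as a success

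*Protocol*

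**What the plan says.** Four places in the protocol bear on how a smoker is scored.

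- **Instruments** gives the purpose of objective measurement: "We will use available objective assessment tools to supplement the participants' self-reported outcomes to determine changes in their health-risk behaviours after the intervention". It continues: "For verifying smoking cessation, we will use the biochemically validated 7-day point prevalence of abstinence", determined by saliva cotinine and exhaled carbon monoxide. The rule is strict: a claimed quitter has to satisfy both limits, and anyone else is taken to have failed. Participants are paid for it, with a HK$200 "supermarket coupon being the incentive for completing biochemical validations".
- **Outcome measures** says that the primary outcome "will be the number of healthy lifestyles adopted at 6 months". It then refers the reader onward: "The criteria of successful adopting a healthy lifestyle are presented in Appendix 1". The secondary outcomes are the same count at 12 months and quality of life at 6 and 12 months. Validated abstinence is not listed.
- **Appendix 1** sets the success criterion for tobacco use as "Self-reported 7-day point prevalence of smoking abstinence". It adds no biochemical condition.
- **Data Analysis** describes the GEE model as giving adjusted odds ratios "for the self-reported the number of healthy lifestyles engaged in". It names no analysis of validated abstinence.

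The protocol does not state when validation takes place, or how a claimed quitter who fails or misses it is scored in the count.

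**The concern.** The cotinine and carbon monoxide tests are the only objective check on any of the four behaviours. Blood pressure and body mass index are also recorded, but they verify no behaviour and enter no success criterion. As the outcome is defined, the test result cannot change anyone's score. A person who reports abstinence and whose samples show otherwise has failed under Instruments and succeeded under Appendix 1.

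Two things are at stake. First, tobacco success has two possible definitions inside the primary outcome, and a choice between them could be made after the results are known. Second, false quit claims count as successes. If they are more common in the intervention arm, they count as treatment effect. That is plausible here. Intervention participants choose a personal goal and are reminded weekly to keep to it, while controls receive general advice only. The follow-up section also has the research assistant assess success by telephone and then coach the next goal. Data Analysis aims for conservative estimates by counting non-responders as failures, and counting a refuted quitter as a success works against that aim.

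**Working it through.** **1. The plan's own sample size.** Inputs from Sample size: 5% versus 10%, two-sided 5%, power 80%, 1:1 allocation. With pooled variance and no continuity correction:

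n = [1.96·√(2 × 0.075 × 0.925) + 0.8416·√(0.05 × 0.95 + 0.10 × 0.90)]² / 0.05² = (0.730 + 0.312)² / 0.0025 ≈ 434.4, so 435 per group, as stated.

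With 30% attrition, 870 / 0.70 = 1,242.9, against 1,242 stated. There is no arithmetic error. The point concerns the outcome definition only.

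**2. One participant under the two rules.** Take a baseline smoker who reports 7-day abstinence at 6 months.

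| Test result | Instruments | Appendix 1 |
|---|---|---|
| Both limits met | validated | adopted |
| Either limit not met | failed validation | adopted |
| Test not done | not validated | adopted |

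The rules part company in the second and third rows, and Outcome measures follows the Appendix 1 column.

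**3. Size of a possible bias (assumed inputs).** The document gives neither the share of smokers nor a false-claim rate. Let s be the share of smokers and e the excess of false quit claims in the intervention arm. Use the binary outcome on which the trial was sized, at least one lifestyle adopted, with 5% success in both arms and no true effect. Only the 95% who are not already successes can be moved by a false claim, so the spurious difference is s × e × 0.95.

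- s = 25%, e = 5 points: 0.25 × 0.05 × 0.95 = 0.0119, or 1.2 points.
- s = 25%, e = 10 points: 0.25 × 0.10 × 0.95 = 0.0238, or 2.4 points.
- Wider range: 0.15 × 0.05 × 0.95 = 0.7 points to 0.40 × 0.10 × 0.95 = 3.8 points.

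These apply among responders. At 435 per group the two-sided rejection rate is 12% for 1.2 points and 31% for 2.4 points.

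Data Analysis, however, keeps everyone randomised (1,242 / 2 = 621 per arm) and sets non-responders to their baseline values. At 30% attrition only 70% can make a claim:

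- 1.19 × 0.70 = 0.8 points; 2.38 × 0.70 = 1.7 points.
- Rejection at 621 per arm, base 5%: 10% and 24%.
- Rejection at 621 per arm, base 0.05 × 0.70 = 3.5%: 12% and 30%.

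**4. Power if validation is required (assumed inputs).** Let f be the share of all counted successes lost, equal in both arms.

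| f | Rates | n per group for 80% | Power at 435 |
|---|---|---|---|
| 0 | 10% v 5% | 435 | 80% |
| 10% | 9% v 4.5% | 487 | 75% |
| 20% | 8% v 4% | 553 | 70% |
| 30% | 7% v 3.5% | 637 | 64% |

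The true f depends on how many successes rest on tobacco alone and how many of those fail validation. The document gives neither.

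**The case against.** The best defence is that Outcome measures, Data Analysis and Appendix 1 agree with one another: the outcome is self-reported. Instruments says that the objective tools supplement self-report, and its rule says who has failed validation, not who is scored as a smoker in the primary outcome. A self-reported outcome with supportive validation is a coherent design, and a sensitivity analysis on validated abstinence could sit in an SAP that is not shown. This part stands: a reader might infer that the protocol flatly defines the primary outcome twice, or that the validation data will certainly go unused, and the text does not go that far. It does not remove the point, because the same section says that validation serves to verify cessation and to determine behaviour change, while the scoring rule in Appendix 1 gives the test no role.

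Three further objections also stand.

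- A reader might take the 1.2 to 2.4 points as an estimate of bias. They rest on assumed inputs and shrink under the planned imputation. The protocol also states that assessors are blinded, and controls receive a similar call and messages at a similar frequency.
- Counting every unvalidated claimant as a failure can itself bias the comparison if attendance for testing differs by arm.
- A reader might think that the change is purely one of wording, or that the whole count could then be called objective. Neither follows. No validation time point is given, follow-up is by telephone, and diet, activity and binge drinking have no objective check.

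**Conclusion.** The point holds as an unreconciled outcome definition with a concrete consequence: under the plan as written, a claimed quitter whose test refutes the claim is a primary-outcome success. This rests on the text alone and needs no assumption. It affects one of four behaviours, but it lies inside the primary outcome, so it should be amended.

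The amount of bias is unknown. On the assumptions in the working, it is about 0.8 to 1.7 points over all randomised participants, against a planned difference of 5 points, with a rejection rate of roughly 10 to 30% when there is no true effect. If false claims are equally frequent in both arms, this mechanism creates no spurious difference, but the conflict over scoring remains. Requiring validation removes only the tobacco part of any reporting bias.

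**What to change.** Reconcile Instruments with Outcome measures, Data Analysis and Appendix 1.

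1. In Appendix 1, count tobacco success at 6 and 12 months only when abstinence is validated under the rule in Instruments. Score refuted claims as not adopted.
2. State the time points of validation and how claimants with no test result are scored.
3. Prespecify two sensitivity analyses: one that varies the handling of missing validation, because attendance may differ by arm, and one on self-report alone.
4. Keep the word self-reported in the GEE sentence for diet, activity and binge drinking, and note there that tobacco is validated.

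If the sponsor prefers self-report as primary, the protocol should say so and name the validated version as a prespecified sensitivity or secondary analysis.

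**Cost.** Testing and its incentive are already planned, but the protocol does not show that they cover both 6 and 12 months, so extra contacts may be needed. There will be fewer tobacco successes and some loss of power. As an illustration, losing 10 to 30% of all successes equally in both arms takes power at 435 per group from 80% to about 75 to 64%. The sample size should be reviewed against the definition chosen.

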#### Subjects

Chinese adults who attend one of the five EDs in various clusters in Hong Kong because of physical discomfort and if they meet the following criteria will be invited to participate. The inclusion criteria will be as follows: (1) being aged  $\geq 18$  years, (2) being triaged as semi-urgent (level 4) or non-urgent (level 5) and discharged home on the same day after receiving medical attention, (3) having at least one health risk behaviour (tobacco use, harmful alcohol consumption, unhealthy diet, and physical inactivity), and (4) owning a smartphone and having an ability to use instant messaging applications (e.g. WhatsApp or WeChat). The Exclusion criteria will be as follows: (1) having a poor cognitive state or mental illness and (2) being diagnosed with NCDs and undergoing regular follow-ups in outpatient clinics, and (3) participating in another related study.

The specific criteria for each health risk behaviour are listed in Appendix 1. People who do not have a smartphone or use WhatsApp/WeChat (unlikely in Hong Kong) will be provided brief advice and a Practical Resource Hub for Healthy Life leaflet on healthy lifestyles but will be excluded from the study.

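### Appendix 1 joins both the inactivity criterion and its success criterion with 'or', so a participant active by one route only is eligible as inactive and can be counted as an adopter without changing

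*Protocol*

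**What the plan says.** Protocol, Appendix 1, physical inactivity row:

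- Risk column: "Performed less than 150 minutes of moderate-intensity aerobic physical activity throughout the week, or (2) performed less than 75 minutes of vigorous-intensity" activity in the week.
- Success column: "Performed at least 150 minutes of moderate-intensity aerobic physical activity throughout the week, or performed at least 75 minutes of vigorous-intensity aerobic physical activity" in the week.

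Protocol, Subjects: an inclusion criterion is "having at least one health risk behaviour", and the reader is told that "The specific criteria for each health risk behaviour are listed in Appendix 1".

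Protocol, Outcome measures: the primary outcome "will be the number of healthy lifestyles adopted at 6 months", with success again defined by Appendix 1.

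Protocol, Appendix 1, unhealthy diet row: risk is "less than five servings of fruit and vegetables per day or have had a daily intake of less than 400 grams" and success is "at least five servings of fruit and vegetables per day or have had a daily intake of at least 400 grams".

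Protocol, Data Analysis: non-responses at follow-up are replaced by baseline values. The protocol explains this as assuming either failure or no change.

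**The concern.** A risk criterion and the matching success criterion should be complements, so that nobody is in both columns or in neither. If success means reaching threshold A or threshold B, the complement is missing A *and* missing B. The protocol writes the risk side with *or*. Only a person who reaches both thresholds then escapes the inactive label, and everyone active by a single route sits in both columns.

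This reaches the two places where Appendix 1 is used. At entry, a person whose only listed risk is this form of inactivity can be enrolled with nothing to change on that behaviour. At 6 months, the same person meets the success criterion by carrying on as before. A participant enrolled for another reason, such as smoking, can likewise gain one adopted lifestyle for activity that was already there at baseline. At stake are the adoption rates in both arms, the difference that the trial is powered to detect, and the number of adopters that feeds the cost-effectiveness analysis.

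**Working it through.** **1. The logic.** Let m be weekly minutes of moderate activity and v weekly minutes of vigorous activity.

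- Risk as written: m < 150 or v < 75.
- Success as written: m ≥ 150 or v ≥ 75.

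| m | v | At risk as written | Success as written | At risk if joined by 'and' |
|---|---|---|---|---|
| 200 | 0 | yes | yes | no |
| 0 | 90 | yes | yes | no |
| 150 | 0 | yes | yes | no |
| 100 | 30 | yes | no | yes |
| 150 | 75 | no | yes | no |

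A grid of m from 0 to 300 in steps of 10 and v from 0 to 150 in steps of 5 has 31 × 31 = 961 points. Both thresholds are met at 16 × 16 = 256 points, so 961 − 256 = 705 are at risk as written. Neither threshold is met at 15 × 15 = 225, so 705 − 225 = 480 are both at risk and a success. With 'and', no point is in both columns and none is in neither. These counts check the logic. They are not population shares.

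**2. The protocol's own sample size** (Sample size section: 10% vs 5%, two-sided 5%, 80% power). With p̄ = 0.075,

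n = [1.960 × √(2 × 0.075 × 0.925) + 0.842 × √(0.10 × 0.90 + 0.05 × 0.95)]² / 0.05² = (0.730 + 0.312)² / 0.0025 ≈ 434.4, rounded up to 435 per group.

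This reproduces the stated figure. Dividing 870 by 0.70 gives 1,242.9, in line with the stated total of 1,242.

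**3. Illustration of dilution.** Assume that a share x of each arm already meets the success criterion at baseline and is scored as an adopter, and that the rest adopt at 10% and 5%. The observed rates become x + (1 − x) × 0.10 and x + (1 − x) × 0.05, so the difference shrinks to (1 − x) × 5 points while the variance rises. The share x is an assumption. Power is for the two-proportion z-test with pooled variance under the null hypothesis.

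| x (assumed) | Intervention | Control | Difference | Power, 435 per arm | n per arm for 80% power |
|---|---|---|---|---|---|
| 0 | 10.0% | 5.0% | 5.0 points | 80% | 435 |
| 5% | 14.5% | 9.75% | 4.75 points | 57% | 741 |
| 10% | 19.0% | 14.5% | 4.5 points | 43% | 1,080 |
| 20% | 28.0% | 24.0% | 4.0 points | 27% | 1,887 |

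**4. Non-response.** For a person with m = 200 and v = 0, the baseline state already meets the success criterion. If the outcome is scored as a state, carrying baseline forward imputes a success. If it is scored as change, carrying baseline forward imputes no change, as the Data Analysis section intends.

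**5. The other rows.** In the diet row the two clauses are two measures of one quantity. Overlap needs both to be recorded for the same person and to disagree, for example 4 servings weighing 450 g. The tobacco and binge-drinking rows do not have this form.

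**The case against.** The best reply is that adoption plainly means change. The Data Analysis section describes the primary analysis in terms of behavioural change at 6 months, the sample-size endpoint speaks of modifying risk behaviours, and the follow-up calls ask about a lifestyle that the participant chose as a target. A pure state reading would also make every baseline non-smoker a success on tobacco, which cannot fit an assumed control rate of 5% or less. That argument is sound against the state reading, but it does not remove the problem. The natural way to code change from Appendix 1 is risk column met at baseline and success column met at follow-up, and that coding still scores the unchanged person at 200 and 0 minutes as an adopter. What stands is that the protocol does not spell out the scoring, so the miscount is what the written columns permit and not something shown to occur.

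It can also be said that this is a wording slip and that the authors meant inactivity as reaching neither threshold. That is plausible, but staff who screen and assess will apply the words as written.

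Four stronger inferences are tempting, and the protocol does not support them:

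- *The comparison is biased towards one arm.* Overlap is fixed at baseline and allocation is random, so it should fall equally on both arms.
- *The planned power is lost.* Every loss in the table depends on x, for which the protocol gives no value. The model is also binary, whereas the primary outcome is worded as a number of lifestyles, and it uses 435 evaluable participants per arm, whereas the planned analysis imputes all non-responders. The table does not describe the planned analysis exactly.
- *The diet row has an equal fault.* Servings and grams measure one intake, and the protocol does not say that both are recorded.
- *The missing-data rule is broken.* It fails for these people only if the outcome is scored as a state, because the rule also allows for no change.

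**Conclusion.** The inconsistency in the physical-activity row is real and follows from the wording alone. Anyone active by a single route is both eligible as inactive and already successful, and nothing elsewhere in the protocol removes the overlap. The expected consequence is a raised adoption rate in both arms and a diluted difference. Its size cannot be fixed from the protocol. If 5% to 20% of participants were in this position, with a binary outcome and the planning rates in the rest, power would lie between about 57% and 27% instead of 80%. The diet overlap is minor, and the conflict with the imputation rule is conditional on how the outcome is scored. The correction belongs in the protocol, because an analysis plan written later could rescore the outcome but could not undo the enrolment of people who had nothing to change.

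**What to change.** In the Appendix 1 risk column for physical inactivity, join the two clauses with 'and', so that risk is the exact complement of success. In Appendix 1 or under Outcome measures, add one sentence: a lifestyle counts as adopted only if its success criterion was not met at baseline and is met at follow-up. That sentence also settles how these people are scored when baseline values are carried forward. Make the same change from 'or' to 'and' in the diet risk criterion for consistency. Apply the amended criteria to both screening and the primary outcome.

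The cost is a two-word change, one added sentence and an updated screening form. Slightly fewer attendees will be eligible. Those active by one route who have another listed risk behaviour can still enter on that behaviour.
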